## Abstract

**Background:**

Women of reproductive age experience cyclical variation in the female sex steroid hormones 17β-estradiol and progesterone during the menstrual cycle that is attenuated by some hormonal contraceptives. Estrogens perform a primary function in sexual development and reproduction but have nonreproductive effects on bone, muscle, and sinew tissues (ie, ligaments and tendons), which may influence injury risk and physical performance.

**Objective:**

The purpose of the study is to understand the effect of the menstrual cycle and hormonal contraceptive use on bone and calcium metabolism, and musculoskeletal health and performance.

**Methods:**

A total of 5 cohorts of physically active women (aged 18-40 years) will be recruited to participate: eumenorrheic, nonhormonal contraceptive users (n=20); combined oral contraceptive pill (COCP) users (n=20); hormonal implant users (n=20); hormonal intrauterine system users (n=20); and hormonal injection users (n=20). Participants must have been using the COCP and implant for at least 1 year and the intrauterine system and injection for at least 2 years. First-void urine samples and fasted blood samples will be collected for biochemical analysis of calcium and bone metabolism, hormones, and metabolic markers. Knee extensor and flexor strength will be measured using an isometric dynamometer, and lower limb tendon and stiffness, tone, and elasticity will be measured using a Myoton device. Functional movement will be assessed using a single-leg drop to assess the frontal plane projection angle and the qualitative assessment of single leg loading. Bone density and macro- and microstructure will be measured using ultrasound, dual-energy x-ray absorptiometry, and high-resolution peripheral quantitative computed tomography. Skeletal material properties will be estimated from reference point indentation, performed on the flat surface of the medial tibia diaphysis. Body composition will be assessed by dual-energy x-ray absorptiometry. The differences in outcome measures between the hormonal contraceptive groups will be analyzed in a one-way between-group analysis of covariance. Within the eumenorrheic group, the influence of the menstrual cycle on outcome measures will be assessed using a linear mixed effects model. Within the COCP group, differences across 2 time points will be analyzed using the paired-samples 2-tailed *t* test.

**Results:**

The research was funded in January 2020, and data collection started in January 2022, with a projected data collection completion date of August 2024. The number of participants who have consented at the point of manuscript submission is 66. It is expected that all data analysis will be completed and results published by the end of 2024.

**Conclusions:**

Understanding the effects of the menstrual cycle and hormonal contraception on musculoskeletal health and performance will inform contraceptive choices for physically active women to manage injury risk.

**Trial Registration:**

ClinicalTrials.gov NCT05587920; https://classic.clinicaltrials.gov/ct2/show/NCT05587920

**International Registered Report Identifier (IRRID):**

DERR1-10.2196/50542

## Introduction

### Background

Women of reproductive age experience cyclical changes in endogenous sex steroid hormones during the menstrual cycle. These hormones regulate and support the production, release, and fertilization of the ovum. 17β-estradiol, the predominant estrogen in women of reproductive age, is produced by the ovaries during the early stages of the menstrual cycle. Progesterone is secreted by the *corpus luteum*—the discarded sac of the ovum—after ovulation and stimulates endometrial growth in preparation for fertilization in the later stages of the menstrual cycle. Growth and release of ova are regulated by the anterior pituitary hormones—follicle-stimulating hormone and luteinizing hormone (LH)—under the influence of gonadotropin-releasing hormone [1].

Hormonal contraceptives (HCs) are made from synthetic forms of estrogens or progesterone, in some instances combined in varying concentrations. They prevent pregnancy by disrupting the release of gonadotropin-releasing hormone, suppressing ovulation, and altering the uterine lining to impair egg implantation. Consequently, the majority of HCs reduce circulating endogenous sex steroid hormones [2]. The most commonly used HC is the combined oral contraceptive pill (COCP), but long-acting reversible contraceptives (LARCs) containing progestin only, administered by subcutaneous implant, intrauterine system (IUS), or intramuscular injection, are increasingly popular methods [3]. Some studies have measured temporal patterns of sex steroid hormones during the menstrual cycle [4] and in COCP users [5,6], but data are lacking in LARC users.

HCs are also used medically to reduce or suppress menstrual bleeding in those experiencing conditions such as endometriosis [7] and by female athletes and servicewomen to delay or prevent menstrual bleeding [8,9]. However, there is growing concern that the noncontraceptive effects of estrogens on bone, muscle, and metabolism may influence injury risk and physical performance [10]. Estrogens are essential to bone health; women who experience conditions with lower estrogens, such as postmenopausal women [11] and those with functional hypothalamic amenorrhea [12], have lower bone mass compared with eumenorrheic (EUM) women. The influence of HCs on bone mass and bone stress injury risk is less clear [13], although biochemical markers of bone resorption and formation are lower in COCP users compared with EUM women [14-16]. The use of the COCP may decrease bone remodeling by a reduction in endogenous estrogens or indirectly by a synthetic estrogen-mediated reduction in *free* insulin-like growth factor I (IGF-I) [17].

Osteogenesis is the formation of new bone tissue performed by osteoblasts. Bone resorption is the process by which osteoclasts break down bone tissue, releasing calcium and other minerals into the circulatory system. Biochemical markers of bone resorption and formation reflect metabolic processes in bone, but they do not provide quantitative data on calcium status. A total of 6 naturally occurring calcium isotopes exist (^40^Ca, ^42^Ca, ^43^Ca, ^44^Ca, ^46^Ca, and ^48^Ca). Bone formation favors the uptake of lighter calcium isotopes and subsequently causes the composition of urine to shift toward an isotopically heavier state [18]. If bone resorption is the dominant metabolic process and calcium is excreted from the bone, the calcium isotopic composition of the urine becomes lighter [19]. Low estrogens increase bone resorption, but the effect of estrogen status on calcium homeostasis (ie, whether calcium is being deposited or lost from bone), measured from ^44^Ca:^42^Ca isotopes, is not known.

Traditionally, bone strength has been inferred from measures of areal bone mineral density (aBMD) with dual-energy x-ray absorptiometry (DXA). DXA is not portable and emits ionizing radiation, and an alternative ultrasound-based method may provide valid hip and spine aBMD measurements that can be used in field-based scenarios. Additionally, peripheral quantitative computed tomography (pQCT; volumetric bone mineral density and structure) and impact microindentation provide additional, and possibly superior, estimates of bone strength in vivo in young adult healthy women compared with DXA [20]. Preliminary data using pQCT in female soldiers indicate differential effects of COCP and non-HC use on tibial adaptations during arduous training [21], with implications for stress fracture risk. High-resolution pQCT (HRpQCT) offers more detailed information on bone strength based on bone microstructure [22]. Hypoestrogenic athletes have poorer bone microarchitecture and higher stress fracture risk compared with their EUM counterparts [12,23], while female military recruits taking progestin-only contraceptives experience blunted tibial adaptations to military training compared with COCP and EUM women [24].

Anterior cruciate ligament injury risk is highest mid-cycle in EUM athletes [25,26], with a lower risk in COCP users [26], suggesting a role of estrogens. In skeletal muscle, estrogens are purported to exert beneficial effects, and low estrogens status can impair muscle strength and growth [27,28]. Menstrual bleeding and HC use can influence iron status, including the prevalence of iron deficiency, through excessive iron loss or by mediating hepcidin production, an acute-phase protein that impairs iron absorption. Understanding the effects of the menstrual cycle and hormonal contraception on musculoskeletal health and performance will inform contraceptive choices for physically active women to manage injury risk.

### Aims and Hypotheses

There is limited evidence for the overarching effects of estrogen on bone and calcium metabolism and musculoskeletal performance and even fewer studies investigating the impact from chronic use of HCs. Our primary aims are to (1) investigate the effect of menstrual cycle phase on bone and calcium metabolism, and musculoskeletal health and performance in EUM, non-HC users (EUM group); and (2) investigate the effects of HC use on bone and calcium metabolism, and musculoskeletal health and function. Our secondary aims are to (1) determine the validity of an ultrasound-based method of measuring hip and spine aBMD compared with “gold standard” DXA and (2) compare calcium and bone metabolism, reproductive hormones, and musculoskeletal function between the pill phase and non-pill phase of COCP use.

This study will test the following hypotheses in 2 study designs. Menstrual cycle phase (within-groups design): (1) calcium and bone metabolism is decreased during the ovulatory phase compared with other phases; and (2) muscle strength and tissue mechanical properties differ across the menstrual cycle. HC use (between-groups design): (1) calcium and bone metabolism is higher in the implant and injection groups compared with IUS (which exerts localized effects) and EUM (ovulatory phase) groups, and lower in the COCP group; (2) estradiol and progesterone are lower in HC users compared with the EUM group during the ovulatory phase; (3) bone macro- and microstructure, muscle strength, and tissue properties are different in HC users compared with the EUM group; and (4) calcium and bone metabolism, reproductive hormones, and musculoskeletal function are different between the pill phase and non-pill phase of COCP use.

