### Measurements

#### Menstrual Cycle Tracking

Menstrual cycle phase and length will be monitored in the EUM group; many participants may already be using a menstrual tracking app, which will aid in cycle prediction using historical cycle length data.

Participants will be asked to report day 1 of menses, and all subsequent laboratory visits will be planned according to their reported cycle length. To verify the predicted phases of the menstrual cycle, the EUM group will be given urine dip stick tests (LH surge test) to test for ovulation between days 10 and 15 of the menstrual cycle for a 28-day cycle to ensure that testing occurs during the ovulatory phase. Women will be scheduled for testing at their *predicted* ovulation but will be *actually* tested once they also produce a positive LH test; we expect these dates to coincide. If a woman does not ovulate during the testing cycle, she will be invited to retest the following month.

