All continuous data will be checked for normality using a Shapiro-Wilk test and by visually checking for skewness and kurtosis. Markers of bone and calcium metabolism, reproductive function, and musculoskeletal health will be compared between contraceptive groups with a one-way between-group analysis of covariance (EUM [day 14] vs COCP [day 21] vs hormonal implant vs IUS vs hormonal injection groups) controlling for age, lean body mass (for bone measures only), physical activity, total 25(OH)D, and previous hormonal injection use. Categorical data from questionnaires will be analyzed using a chi-square test to test for differences between lifestyle, prior HC use, menstrual cycle history, and dietary choices between groups. Nonnormally distributed data will be tested using a Kruskal-Wallis test. Significant main effects of the group will be followed up with post hoc 2-tailed *t* tests with a Bonferroni correction (or Mann-Whitney *U* test for nonparametric data). Paired-sample 2-tailed *t* tests will be used to compare markers of bone and calcium metabolism, and reproductive and musculoskeletal function across the 2 time points in COCP users. Markers of bone and calcium metabolism, reproductive function, and muscle strength and tendon function will be compared between days in the menstrual cycle for the EUM group with a linear mixed effects model with the restricted maximum likelihood estimator to allow incorporation of incomplete data. Time will be the fixed effect (day 1 vs day 7 vs day 14 vs day 21), and a random intercept will be assigned to participants to account for the nonindependence of repeated measures. The significance of the fixed effects from each model will be determined with Sattherwaite degrees of freedom. The normality of the residuals for each model will be checked visually by plotting the residuals against the fitted values and from Q-Q plots. In the event of a significant main effect of time, pairwise comparisons with Holm-Bonferroni corrections and Kerward-Roger degrees of freedom will be used on the linear mixed effects model to identify differences between time points. A Bland-Altman plot will be used to assess the agreement between aBMD measured by ultrasound and DXA. Differences will be considered statistically significant at an α level of *P*<.05 with post hoc *P* values corrected for multiple comparisons.

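### Progesterone in contraceptive users is compared with the EUM ovulatory visit, before the protocol expects luteal secretion; the same visit is the expected low point for bone and calcium markers

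*Protocol article*

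**What the plan says.** **Reference visit.** The Statistical Analyses section of the protocol article sets the between-group ANCOVA as "EUM [day 14] vs COCP [day 21] vs hormonal implant vs IUS vs hormonal injection groups". EUM women have four visits, but only the ovulatory one enters this comparison. Under Menstrual Cycle Tracking, women are "tested once they also produce a positive LH test; we expect these dates to coincide".

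**Hormones.** Between-group hypothesis (2) in Aims and Hypotheses states that "estradiol and progesterone are lower in HC users compared with the EUM group during the ovulatory phase". The Background says that estradiol "is produced by the ovaries during the early stages of the menstrual cycle". It says that progesterone is secreted by the corpus luteum "after ovulation and stimulates endometrial growth in preparation for fertilization in the later stages of the menstrual cycle".

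**Bone and calcium.** Within-cycle hypothesis (1) states that "calcium and bone metabolism is decreased during the ovulatory phase compared with other phases". Between-group hypothesis (1) states that "calcium and bone metabolism is higher in the implant and injection groups compared with IUS (which exerts localized effects) and EUM (ovulatory phase) groups", and that it is lower in the COCP group.

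**Samples available.** Table 1 lists progesterone, the bone turnover markers and the calcium measures at four EUM time points. Venous Blood and Urine Sampling includes a midluteal draw (day 21 of a 28-day cycle). LARC users are measured once, with no cycle timing.

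**The concern.** Two separate problems follow from using one EUM visit as the reference.

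First, hypothesis (2) treats estradiol and progesterone alike, although the protocol gives them different timing. On its own account, the ovulatory visit falls before luteal progesterone secretion or at its very start. A contraceptive could abolish the luteal rise completely and still differ little from EUM women at that visit. A null progesterone result would then say little about suppression.

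Second, if within-cycle hypothesis (1) is true, day 14 is the lowest EUM value for bone and calcium metabolism. Every contraceptive-versus-EUM contrast on those markers is then shifted upwards by the depth of the dip. This pushes implant and injection towards appearing higher than EUM and works against finding COCP lower. Primary aim 2 concerns the effects of contraceptive use in general, and the Discussion says the results will inform contraceptive choice, so a phase-specific difference could be read too broadly.

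**Working it through.** **1. Progesterone: the passages side by side**

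- Trigger of the reference visit: a positive LH test (Menstrual Cycle Tracking).
- Timing of secretion: after ovulation, in the later part of the cycle (Background).
- Hypothesis and test: contraceptive users lower than EUM at the ovulatory visit (Aims and Hypotheses; Statistical Analyses).
- Unused alternative: the midluteal draw, with progesterone assayed at all four EUM visits (Venous Blood and Urine Sampling; Table 1).

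The documents give no progesterone values by phase, so the size can only be illustrated. With 20 versus 20 and a two-sided t test on 38 df, under assumed differences:

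| Assumed EUM-minus-HC difference | Power at 0.05 | Power at 0.005 |
|---|---|---|
| 0-0.3 SD (ovulatory reference) | 5%-15% | 0.5%-3% |
| 1.0-1.5 SD (midluteal reference) | 87%-99.6% | 58%-95% |

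**2. The plan's own figure**

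Statistical Analyses gives 8 to 17 participants for the within-EUM time effect (7 time points, eta squared 0.06-0.14, alpha 0.05, power 0.80). Take f² = η²/(1−η²) and noncentrality λ = f²·N·m/(1−ρ), with m = 7. Assume ρ = 0.5 and no sphericity correction, neither of which is stated.

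- η² = 0.06: N = 17 (power 0.82; N = 16 gives 0.79).
- η² = 0.14: N = 8 (power 0.86; N = 7 gives 0.79).

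The figure reproduces exactly. It does not depend on the reference visit, so this point neither supports nor overturns it. The match does suggest that f is on the per-visit SD scale, which is used next.

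**3. Bone and calcium: how far day 14 could sit from the cycle mean**

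Assumption (worst case): the whole planned phase effect is a dip of D SD at one of the four visits. Day 14 is then 0.75D below the cycle mean and each other visit 0.25D above it. So f² = [(0.75D)² + 3(0.25D)²]/4 = (3/16)D², and D = f/0.433.

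| η² | f | D | 0.75D | Noncentrality 0.75D·√10 |
|---|---|---|---|---|
| 0.06 | 0.2526 | 0.58 | 0.44 | 1.38 |
| 0.14 | 0.4035 | 0.93 | 0.70 | 2.21 |

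**4. Chance of declaring a difference when the contraceptive group equals the EUM cycle mean**

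Two-sample t test, 20 versus 20, 38 df, equal SD. Five groups give 10 pairs; if all are compared, Bonferroni alpha is 0.05/10 = 0.005.

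| η² | At 0.005 | At 0.05 |
|---|---|---|
| 0.06 | 6.8% | 27% |
| 0.14 | 23.9% | 58% |

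**5. The opposite direction: COCP**

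Assume a COCP group truly 0.9 SD below the EUM cycle mean. Against that mean, at equal SD, power is 79% at 0.05 and 46% at 0.005. Against day 14 the visible difference shrinks to 0.90 − 0.44 = 0.46 SD or 0.90 − 0.70 = 0.20 SD. Power becomes 30% or 10% at 0.05, and 8% or 1% at 0.005.

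**The case against.** The best defence is that, for bone and calcium, hypothesis and analysis agree: both name the ovulatory phase. A single LH-confirmed phase is a defensible contrast in a study built around estrogens, and replacing it with a cycle mean would change the estimand. This stands, and it is why the day-14 comparison should stay. The rejections in step 4 are not false positives for the hypothesis as written; they become misleading only when the result is read as a general effect of contraceptive use.

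The mixed model across the four EUM visits will also estimate any dip. That makes the confounding visible but does not remove it from the group contrast.

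The magnitude is a worst case. It assigns the whole assumed effect to one visit, and carries a range set for calcium balance at 7 time points over to 4 visits and to bone markers. Since the plan corrects post hoc tests by Bonferroni, 7%-24% is the relevant range, not 27%-58%.

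A reader might infer that all group comparisons use the wrong reference. The documents do not support that:

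- Only 4 of the 10 pairs involve EUM. The prediction that implant and injection exceed IUS does not use EUM, so the dip alone could not confirm hypothesis (1) in full.
- Hypothesis (4) is within COCP users, and indentation is done outside the main visit schedule.
- DXA, ultrasound and HRpQCT are scheduled on day 14 for EUM, but nothing in the text suggests that structure shifts within a cycle.
- Estradiol is placed before ovulation, so day 14 is not shown to be wrong for it.
- For muscle and tissue outcomes the protocol predicts a difference across the cycle without a direction, so no direction of bias follows.

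Nor can one say that progesterone is at its floor at the visit: the article gives neither values by phase nor the interval from LH test to blood draw.

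**Conclusion.** The progesterone half of hypothesis (2) is tested at a visit where the protocol's own physiology predicts little difference, while a better-placed sample is already collected. This rests on the text alone; the power figures only illustrate it under assumed differences.

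The bone and calcium point holds in a smaller form. If within-cycle hypothesis (1) is right, contrasts with EUM mix phase with contraceptive effect, towards implant and injection being higher than EUM and against COCP being lower. The size is at most about 7%-24% spurious differences per contrast relative to the cycle mean. That assumes the planned eta squared is entirely an ovulatory dip, equal SDs, 20 per group and Bonferroni over 10 pairs. It limits what the day-14 contrast can be said to show; it does not contradict the stated hypothesis.

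**What to change.** 1. Reword between-group hypothesis (2) and the ANCOVA paragraph so that progesterone in contraceptive users is compared with the EUM midluteal visit (day 21 of a 28-day cycle). Keep day 14 for estradiol.
2. For bone turnover and calcium markers, keep the day-14 comparison and add a prespecified sensitivity analysis against the EUM mean over the four visits. Use unequal-variance standard errors, because a four-visit mean has less within-woman variance than a single visit.
3. State that conclusions from the day-14 contrast on these markers apply to the ovulatory phase.

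The cost is a wording change and slightly more analysis. No new visits or samples are required.

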## Methods

### Recruitment

Biochemical markers of bone and calcium metabolism and measures of musculoskeletal health and performance will be obtained in physically active women who are EUM (n=20) or HC users taking or administered COCP (n=20), implants (n=20), IUS (n=20), or hormonal injections (n=20). Participants will be aged 18-40 years; have stable body mass (defined as no change in self-reported body mass ≥5% over the previous 3 months); have a BMI between 18 and 30 kg/m^2^; have a regular menstrual cycle of 24-35 days in length; have not been taking any HC in the last 12 months (EUM group); have used the COCP for at least 12 months (COCP group); have used the IUS continuously for at least 2 years (IUS group); have used the implant continuously for at least 12 months (implant group); or have used the hormonal injection continuously for at least 2 years (injection group). Participants will be excluded if they have diagnosed premature ovarian insufficiency; are pregnant; are less than 2 years post partum; have given birth to more than 2 children; demonstrate evidence of disordered eating (defined as ≥20 on the Eating Attitudes Test-26 items) or have a self-reported eating disorder; report menstrual disturbance (amenorrhea or oligomenorrhea: <9 menstrual cycles in previous 12 months); are a habitual smoker (defined as ≥10 cigarettes per day); are taking any medication known to affect bone or calcium metabolism (eg, treatment for thyroid disorders); have a self-declared history of heart, liver or kidney disease, diabetes or thyroid disorder; self-report a bone injury in the previous 12 months; or have a total 25-hydroxyvitamin D (25(OH)D)<30 nmol/L at prescreening. Finally, any participants not in the injection group who report a history of using the hormonal injection will also be excluded from participation. We will aim to recruit matched sample sizes; however, some HC options are less common, and the study may be unable to achieve the desired sample size. Researchers have stated an end point for data collection of August 2024, giving 2.5 years of recruitment. If any group is underpowered, the sample achieved will be presented to mitigate influences from different time periods. An overview of the study schedule is illustrated in Figure 1; proposed biochemical markers of reproductive health and bone health are listed in Table 1.

